**Methods and analysis:**

This multicentre, parallel-group, randomised controlled trial will evaluate self-directed ACET in 60 individuals with subacute SCI (<6 months postinjury). All participants will receive standard in-patient rehabilitation; the intervention group will additionally undertake a progressive ACET protocol for 8 weeks. Assessments will occur at baseline (T0), 4 weeks (T1), postintervention (T2) and 6-month follow-up (T3). Outcomes include static and dynamic sitting balance with kinematic measurements and high-density electromyography of the erector spinae, corticospinal excitability, muscle strength, functional independence and questionnaires of neuropathic pain, psychological well-being, self-efficacy and motivation, physical activity and health-related quality of life. Quantitative data will be analysed using mixed-model repeated measures ANOVAs and Student’s t-tests. Thematic analysis will be conducted on qualitative data obtained from focus groups in which the feasibility, enablers and challenges of ACET for individuals with subacute SCI will be discussed.

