### Study population and sample size

The sample size was based on the effect size drawn from the feasibility study reporting an improvement in angular displacement of the trunk during forward reaching with ACET compared with the standard of care, with a large effect size (Cohen’s d = 0.85). An a priori power calculation suggested that a sample size of 46 patients with SCI, 23 in each group, is sufficient to detect a between-group difference for the primary outcome measure, using an independent t-test with 80% power and a 5% level of significance. To account for a 6-month follow-up after discharge, a 30% conservative dropout rate was considered. Hence, 60 participants in total will be recruited for this study.

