
### Assessments

The study has four assessment periods—baseline (T0), 4 weeks (T1), postintervention (T2), and 6 months follow-up (T3). Assessments from T0 to T2 are expected to occur while participants are still within 12 months postinjury. However, the T3 assessment may occur during the chronic phase of SCI for some participants. We expect that all participants will have the baseline and 4 weeks assessments conducted at the spinal units. We also anticipate some participants will have the postintervention and 6 months follow-up assessments at the spinal units or at the University of Birmingham, whichever is more convenient to them.

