### Randomisation

All participants will undergo one baseline assessment and one 4-week assessment to estimate individuals’ spontaneous recovery rate. After the 4-week assessment, participants will be randomly allocated (1:1) to an ACET group or a standard care control group using a minimisation randomisation^41^ to balance covariates of level of injury and classification of injury between groups. The procedure will start from the first participant being allocated to a study group at random. For each subsequent participant, we determine which study group would lead to better balance between the groups in the variables of interest. The randomisation will be performed by [name] who will not be involved in recruitment of participants. However, it is not achievable in this study to blind participants or researchers conducting the assessments given the type of the intervention and resources available. Figure 1 illustrates the trial flow chart.

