### Statistical analyses

Statistical analyses will be performed using the latest version of SPSS available at the time of analysis (IBM, Armonk, NY, USA). The distribution of the continuous variables will be tested for normality using the Shapiro-Wilk test and appropriate descriptive parameters will be reported and statistical tests will be applied accordingly. A mixed-model two-way repeated measures ANOVA, with group as the between-participant factor and time as the within-participant factor, will be used to compare outcome measures. This analysis will be performed according to the intention to treat approach. Post hoc tests will be applied where there is a main effect. Significance level will be set at 0.05 for all statistical tests. For the data that are normally distributed, effect sizes of partial eta squared (η2p) or Cohen’s d will be calculated. Additionally, potential confounders (eg, age, days since injury) will be included in the analysis. Subgroup analyses (eg, based on AIS classification) will also be performed if appropriate.

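### The plan claims intention to treat but names a repeated-measures ANOVA that, as usually run over all four visits, keeps only participants with complete data: about 42 of 60 at its own 30% loss allowance

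*Protocol article*

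**What the plan says.** The Statistical analyses section of the protocol article gives one model for comparing outcomes: "A mixed-model two-way repeated measures ANOVA, with group as the between-participant factor and time as the within-participant factor". Of that model it says: "This analysis will be performed according to the intention to treat approach". The same section names SPSS and says that, for normally distributed data, "effect sizes of partial eta squared (η2p) or Cohen’s d will be calculated". The abstract's methods paragraph adds t-tests: "Quantitative data will be analysed using mixed-model repeated measures ANOVAs and Student’s t-tests".

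The Assessments section sets four visits: T0, T1 at 4 weeks, T2 after the intervention and T3 at 6 months. Table 1 schedules the sitting-balance tasks, which belong to the primary outcome, at all four. Under Randomisation, allocation follows T1: "After the 4-week assessment, participants will be randomly allocated (1:1) to an ACET group or a standard care control group". Under Study population and sample size, 46 evaluable participants become 60 because, with the 6-month follow-up in view, "a 30% conservative dropout rate was considered".

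**The concern.** A between/within design, the label ANOVA and partial eta squared together point to the classical mixed-design ANOVA. That method needs a value at every level of the time factor, and as usually run it removes any participant who lacks one. Intention to treat means keeping randomised participants in the analysis, in their allocated arm. Once visits are missed, the named method does not deliver the population claimed for it, and the plan itself allows for substantial loss around T3.

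Two things are at stake. The first is information: a participant seen at T0, T1 and T2 but not at T3 would drop out of the T2 comparison although the T2 value exists. The second is the protection given by randomisation: the T2 comparison would rest on people who return six months later. Allocation is known to participants and assessors, and the added training is effortful and largely unsupervised, so reasons for leaving could differ between arms. If they also depend on how people responded, the completers' estimate is biased.

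**Working it through.** **Inputs.** From Study population and sample size: d = 0.85, independent t-test, 5% level, 80% power, 46 evaluable (23 per group), 30% dropout, 60 recruited. The section does not state sidedness; the two-sided test reproduces its figure. From Assessments and Table 1: four visits for the sitting-balance tasks.

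**Step 1: reproduce the plan's figures.** With n per arm, the noncentrality is λ = d × √(n/2). Power is the probability that a noncentral t with 2n − 2 degrees of freedom and noncentrality λ exceeds the two-sided 5% critical value in absolute size. Solving for 80% gives n = 22.73, so 23 per arm and 46 in total, as stated. Power at 23 per arm is 80.5%. A one-sided test would need 17.83, so 18 per arm, and does not reproduce the figure. The 60 comes from 46 × 1.3 = 59.8.

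**Step 2: count complete cases.** If all four visits enter and 30% lack T3, then 60 × 0.30 = 18 leave the model and 60 × 0.70 = 42 remain, or 21 per arm.

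**Step 3: power by the plan's own t-test at d = 0.85.**

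| Loss from 60 | Analysed | Per arm | λ | Power |
|---|---|---|---|---|
| 0% | 60 | 30 | 3.292 | 89.9% |
| 10% | 54 | 27 | 3.123 | 86.5% |
| 20% | 48 | 24 | 2.944 | 82.2% |
| 30% | 42 | 21 | 2.754 | 76.7% |

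The article does not say how much of the 30% falls before T2. If 10% lacked T2 data (an assumption), 54 would have a T2 value and the complete-case ANOVA would set aside 54 − 42 = 12 of them. At 20% it would be 48 − 42 = 6. If all the loss fell before T2, no T2 value would be discarded. If a further 5% to 10% of those remaining missed some other visit (again an assumption), 42 × 0.95 = 39.9 to 42 × 0.90 = 37.8 complete cases would remain, with power of 74.4% to 72.0%.

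**Step 4: bias, by an illustrative simulation.** The assumptions are SD 1, a correlation of 0.6 between visits, a true difference of 0.85 at T2 and T3, and 27% to 30% lost at T3, with the chance of loss depending on the T2 value as stated in each line. The T2 difference among completers was:

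- loss at random: 0.85
- low responders more likely to leave, equally in both arms: 0.85
- low responders more likely to leave in the ACET arm only: 1.10
- low responders more likely to leave in the ACET arm, high responders in the control arm: 1.36

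These figures show the direction and possible size of the bias. They are not a forecast for this trial.

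**The case against.** A reader might infer that the plan fixes a completers-only analysis. The documents do not support that. No sentence says that incomplete cases are removed, and the term mixed-model is not defined; SPSS can also fit a likelihood-based mixed model that keeps partial data. Missing-data handling may stand in an analysis plan or full protocol that is not shown, and its absence from the article is no fault. This stands. The point is therefore about the method that is named, and is conditional on how it is run.

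The visits entering the ANOVA are also not stated. Table 1 shows that they vary by outcome, the first objective concerns balance after 8 weeks of training, and the abstract also plans t-tests. An ANOVA limited to T0–T2, or a t-test at T2, would keep people who miss only T3. This stands too, although the primary sitting-balance tasks are scheduled at all four visits and the text sets no such limit.

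On size, 30% is described as conservative, and at 20% loss even complete cases give 82.2% power. The calculation uses the plan's t-test, so it is not the power of a group-by-time test. The 60 counts recruits, while allocation comes after T1, so losses before T1 are not losses of randomised participants. The fall from 46 to 42 also reflects how dropout was added: 46 × 1.3 gives 60, whereas 46/0.70 = 65.7 would give 66. That is a separate matter, and the mixed model would not restore missing T3 values. What belongs to the ANOVA is the discarding of observed T2 data.

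Finally, bias needs loss that is related to outcome and differs between arms, and the documents give no evidence that this will happen.

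These limits narrow the point but do not remove it. If a linear mixed model was intended, the text misnames it. If the classical ANOVA was intended, it does not match the intention-to-treat statement once visits are missed.

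**Conclusion.** The point holds in conditional form. The named method, as usually run with all four visits and no imputation, does not deliver the intention-to-treat analysis that the plan claims for it. At the plan's own 30% allowance, about 42 of 60 (21 per arm) would be analysed, with 76.7% power against the stated 80%. With 10% missing at T2, 54 would be available, with 86.5% power.

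This rests on five assumptions: the classical ANOVA is meant; all four visits enter; all 60 recruited are randomised; loss is equal in the two arms; and the t-test stands in for the ANOVA's group comparison. The 10% at T2 is an assumption and not a figure from the article. Bias in the completers' estimate is a possibility that the design leaves open, not a demonstrated result.

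**What to change.** Replace the repeated-measures ANOVA with a likelihood-based linear mixed model, for example the MIXED procedure in SPSS. Include every randomised participant in the allocated arm and all available post-randomisation data (T2 and T3). Enter the T0 and T1 values as covariates, which is valid because both precede allocation. Report the adjusted group difference at T2 with its 95% confidence interval. State that the model assumes data are missing at random, and keep the complete-case ANOVA as a sensitivity analysis.

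The choice of covariance structure, and whether partial eta squared is also reported, are optional and not needed to resolve the conflict. The cost is a change of wording and slightly more analysis work, with the same data and software.

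### The follow-up tests are triggered by a main effect, although with randomisation after T1 the group main effect is a diluted test of ACET and the time main effect is not a comparison of arms

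*Protocol article*

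**What the plan says.** The Statistical analyses section states the model: "A mixed-model two-way repeated measures ANOVA, with group as the between-participant factor and time as the within-participant factor, will be used to compare outcome measures". The only follow-up rule it gives is "Post hoc tests will be applied where there is a main effect". The group by time interaction is not mentioned, no visit is named for the primary comparison, and every test is run at 0.05.

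The Assessments section lists four visits: T0 (baseline), T1 (4 weeks), T2 (post-intervention) and T3 (6-month follow-up). The Randomisation section says "After the 4-week assessment, participants will be randomly allocated (1:1) to an ACET group or a standard care control group". It gives the purpose of the two earlier visits: "All participants will undergo one baseline assessment and one 4-week assessment to estimate individuals’ spontaneous recovery rate". Table 1 nevertheless lists T1 among the post-allocation visits, which conflicts with that text.

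The sample size section assumes d = 0.85 between groups and arrives at 23 per group "using an independent t-test with 80% power and a 5% level of significance". The abstract adds Student's t-tests to the ANOVAs but does not say which contrast they test.

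**The concern.** In this design the ACET effect is a difference between arms that can arise only after allocation. It appears in the group by time interaction or, more directly, in the between-group contrast at T2. The written rule depends on two other terms.

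- **Group main effect.** This averages the arm difference over all four visits, and at two of them the expected difference is zero because allocation has not yet happened.
- **Time main effect.** This averages over arms. The protocol itself expects spontaneous recovery, so a time effect is likely whether or not ACET works, and it does not compare the arms.

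Two errors become possible. If comparisons of the arms wait for a group main effect, a real ACET effect can be missed. If a time main effect opens the gate, unplanned arm comparisons at several visits or within-arm changes can be read as evidence of training. Assessors are unblinded, so the choice of contrast should not be left until the data are in.

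**Working it through.** **Inputs.** From the protocol: d = 0.85, 23 per arm, alpha 0.05, four visits, randomisation after T1. Assumed, because the protocol gives no figures: two-sided tests, equal SDs, compound symmetry with visit correlation ρ = 0.5-0.8, the recovery rate, and how far the effect persists to T3.

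**1. The protocol's own figure.** A two-sided independent t-test at d = 0.85 and 80% power needs 22.73, so 23 per group, and has 80.5% power. The stated 23 per group is reproduced.

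**2. Group main effect.** This is a t-test on each participant's four-visit mean, whose SD is √((1 + 3ρ)/4).

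- Effect at T2 and T3: (0 + 0 + 0.85 + 0.85)/4 = 0.425 SD.
- Effect at T2 only: (0 + 0 + 0.85 + 0)/4 = 0.2125 SD.
- At ρ = 0.6 the SD is √(2.8/4) = 0.837, so the standardised effects are 0.425/0.837 = 0.508 and 0.2125/0.837 = 0.254.

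| ρ | Power, effect at T2 and T3 | Power, effect at T2 only |
|---|---|---|
| 0.5 | 43% | 15% |
| 0.6 | 39% | 13% |
| 0.7 | 36% | 13% |
| 0.8 | 33% | 12% |

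**3. Time main effect without any ACET effect.** Assume both arms recover 0.2 SD per visit, giving means 0, 0.2, 0.4 and 0.6 around 0.3. The sum of squares is 0.09 + 0.01 + 0.01 + 0.09 = 0.20. The noncentrality is 46 × 0.20/(1 − ρ): 18.4 at ρ = 0.5, 23.0 at 0.6 and 46.0 at 0.8. On 3 and 132 df the effect is significant in 96%, 98.6% and nearly 100% of trials.

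**4. What follows once the gate is open.** Null trials were simulated (20,000 per scenario, 23 per arm) with recovery of 0.25 SD per visit in both arms, no ACET effect, and ρ = 0.5, 0.7 and 0.8.

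- Gate open: 99.8-100%.
- Unadjusted between-group test significant at T2 or T3: 7.6-9.0%.
- Within-ACET change from T1 to T2 significant: 21-44%.
- Change significant in the ACET arm but not in the control arm: 17-25%.
- Interaction significant: about 5%, as it should be.

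**5. The same simulation with a true effect of 0.85 SD.** If arm comparisons follow any open gate, T2 or T3 is significant in 88-92% of trials when the effect persists and in 82-83% when it is at T2 only. If they follow only a significant group main effect, T2 is reached and significant in 34-42% and 12-14%.

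**6. A named T2 contrast.** ANCOVA on T1 has standardised effect 0.85/√(1 − ρ²). At ρ = 0.6 this is 0.85/0.8 = 1.0625, with 94% power. With T1 and T0, R² = 2ρ²/(1 + ρ) = 0.72/1.6 = 0.45, so 0.85/√0.55 = 1.146, with 97% power. For ρ = 0.5-0.8 the two-covariate version has about 93% to 99.9%.

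**The case against.** The strongest reply is that the term may be loose wording. A two-way ANOVA contains the interaction as a standard term, SPSS prints it by default, and nothing in the protocol forbids interpreting it. Its power is 89-98% at ρ = 0.6, depending on how far the effect persists. That may well be the intention, but the only written trigger is a main effect, and the interaction is never named.

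A reader might also infer more than the protocol supports:

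- **That neither main effect tests ACET.** This is too strong. Under randomisation the group main effect is a valid 5% test, of an effect cut to a half or a quarter. The time effect carries half of any ACET effect, though it cannot separate that from recovery.
- **That 12-43% is the power of the whole procedure.** It is not. Either main effect opens the gate, and the post hoc contrasts are undefined. The low figures describe the group main effect alone; step 5 shows how much depends on the reading.
- **That the T0 and T1 measurements are wasted.** They enter the ANOVA as levels of time, and the interaction benefits from them. Covariate adjustment is the more direct use, not the only one.
- **That t-tests are not planned.** The abstract plans them. What is missing is the contrast they test, so the sample-size calculation is not linked to a named primary test.

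Table 1 is a further limit. If T1 were post-allocation, only T0 would precede randomisation and the dilution figures would change. The Randomisation text is the more explicit. On either reading T0 dilutes the group effect and the time effect includes recovery.

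**Conclusion.** The concern holds as a fault in a stated decision rule, not as a missing detail. The gate depends on main effects: one dilutes the ACET effect to 0.43 or 0.21 SD (power about 33-43% or 12-15%, against 80.5% for the t-test that sized the trial), and the other is significant in 96-100% of trials under an assumed recovery of 0.2 SD per visit. Once the gate is open, undefined and unadjusted follow-up at T2 and T3 gives about 8-9% false positives, and within-arm comparisons can mislead far more often.

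The correlations, compound symmetry, recovery rates and persistence at T3 are assumptions. The direction of the result does not depend on their exact values, but the gate's near-certain opening does need some recovery. The point applies to outcomes measured at all of T0-T3, which include the primary ones. It does not apply to the SF-36, LTPAQ-SCI, SCIM-III or accelerometry. It bears on the primary conclusion and should be settled before analysis.

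**What to change.** - Delete the main-effect trigger.
- State the primary test as the between-group difference at T2 with a 95% CI, from ANCOVA or a linear mixed model with post-randomisation visits as outcomes and T1 and T0 values as covariates.
- Report the T3 difference as secondary, from the same model.
- State that neither the group nor the time main effect will be read as evidence for ACET, and that within-arm changes are descriptive.
- Say which contrast the t-tests in the abstract address, and link the sample-size calculation to the named primary test.
- Reconcile Table 1 with the Randomisation section on whether T1 precedes allocation.

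The cost is wording only. The measurements are already scheduled, no extra participants are needed, and under the assumptions above power at T2 rises from 80.5% to about 97% at ρ = 0.6.

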### Safety

Exercise intervention and neurophysiological and behavioural assessments are considered as of low risk. Potential risks relating to the study participation are stated in the participant information sheet and will also be verbally explained to the potential participant to ensure that they are fully informed before providing written consent. Any study-related adverse or serious adverse events will be documented and reported in accordance with the Sponsor’s safety reporting procedures.

### Data management

Information with regards to study participants will be kept confidential and managed in accordance with the Data Protection Act 2018, General Data Protection Regulation (GDPR), The UK Policy for Health and Social Care and Research Ethics Committee Approval. Data generated by this study will be kept for 10 years as per University of Birmingham guidelines including the patient consent forms. Data will be stored on secure, encrypted university servers and accessed only by the research team using 2-factor authorisation. No data will be stored on laptops or portable drives.

## Discussion

Evidence generated from this study may influence the current in-patient rehabilitation care post-SCI in the National Health Service in the United Kingdom. Trunk rehabilitation is important for regaining function and independence of individuals after SCI, but it requires high levels of input and supervision from professionals, reducing the time that patients can spend on the rehabilitation, thereby hindering recovery trajectory. Our ACET programme is a self-directed intervention and uses simple equipment that can be easily set up in a clinical environment. Our programme, therefore, has the advantage of being simply delivered alongside the standard of care. Using the comprehensive outcome measurements our study will address the effects of the intervention, but also the mechanisms underpinning the effects of the intervention, and long-term benefits to the individuals with SCI. Moreover, this study will provide insight into factors promoting participation in such an exercise intervention as well as barriers to engagement that are important for optimising adherence to future exercise interventions in individuals with SCI. Taken together, the results have the potential to contribute to the development of personalised treatment plans for recovery after SCI and to provide broader implications for trunk rehabilitation in other clinical populations, such as stroke survivors, amputees and ageing.
